## Methods

### Ethical Considerations

In conducting this study, careful attention was given to the ethical considerations that guide the treatment of research participants, ensuring the protection of their rights, privacy, and well-being throughout the study.

The study was conducted in accordance with the Declaration of Helsinki, and the protocol was approved by the University of California, Irvine, Institutional Review Board (UCI IRB #1596).Informed consent: All participants gave their informed consent for inclusion before they participated in the study.Privacy and confidentiality protection: All identifiable data collected were removed and replaced with a code. A securely maintained list links this code to the identifiable information, and is kept separately from the research data. All research data are maintained in a secure location at the University of California, Irvine, to which only authorized individuals have access. The data are stored electronically on a cloud and an external drive in an encrypted, password-protected file. Video or audio recordings are stored in a secure location; these data are transcribed and deidentified before analyses.Compensation: The CSPs are compensated for their participation in the study, with compensation broken down as follows: US $30 for baseline visit 1, US $40 for baseline visit 2 (waitlist control group only), US $25 for each intervention session (total US $100), US $40 for posttreatment session, and US $50 for the follow-up visit. Overall, participants can earn US $220 or US $260 depending on the assigned group (experimental vs control). Participants can choose to receive the compensation via Venmo (PayPal, Inc) or as a physical or web-based gift card.

### Eligibility Criteria and Recruitment

All participants will be CSPs employed at partner community health agencies, including Latino Health Access (LHA), Dignity Health, and other agencies, to be recruited throughout our enrollment period. Participating agencies and CSPs will serve HL communities and will be located throughout the United States. Inclusion criteria include being aged ≥18 years and working (for payment or as a volunteer) as a CSP serving low-income HL families. Given that this pilot study is intended to test RS on a new population, we identified a sample size (n=80) that would allow us to identify a signal but not a statistically significant (P<.05) effect. This study aimed to generate a pilot study that could be used to support an adequately powered randomized controlled trial.

Participants will be recruited both offline and via email through their agencies, which will post advertisements in English and Spanish at their facilities, announce the opportunity in staff meetings and via email, and facilitate introductions between the research team and the CSPs. Interested participants will contact research personnel.

### Randomization and Overview

In this randomized controlled waitlist design (ClinicalTrial.gov identifier NCT05560893), the CSPs will be randomly assigned to an experimental group or a waitlist group. Both groups will complete an identical assessment battery (assessing health behaviors and psychological well-being) and complete stressor tasks (assessing cardiometabolic risk) before the intervention, after the intervention, and at a 3-month follow-up. The experimental group will receive the RS intervention (4 sessions, 1/wk) 1 week after the baseline assessment (Figure 1). The waitlist group will complete the baseline assessment, wait 4 weeks, complete a second baseline assessment, and 1 week later receive the RS intervention. After completing the RS intervention, the participants in both the experimental and waitlist groups will complete the postintervention assessment 1 week later and a follow-up 3 months later.

**Figure 1 figure1:**
[figure not shown]
Randomization and timeline.

### Measures

#### Primary Outcomes

All the constructs and measures assessed are summarized in Table 1.

All assessments are available in both English and Spanish. Cardiometabolic health, as indicated by cardiometabolic risk and cardiometabolic health behaviors, will be the primary outcome and will be measured before the intervention, after the intervention, and at the 3-month follow-up. Cardiometabolic risk will be measured via HRV in response to a stressor task. The stressor task will consist of a discrimination stream-of-consciousness (SOC) task [35,36], where participants will talk for 4 minutes about an occasion where they felt discriminated against. Before completing the SOC task, participants will complete a questionnaire [36] that will provide them with a list of commonly occurring discrimination events from which they can select an event that has occurred to them. Vagally mediated HRV will be calculated from the variability of the interbeat intervals obtained from electrocardiogram (ECG) data. ECG data will be recorded using a Polar Verity Sense heart rate monitor or Movisens device, small wearable devices that the participants will place in their arm or chest, respectively, during the stressor task and at rest (before and after the stressor task baseline measures). Favorable cardiometabolic health behaviors include behaviors pertaining to sleep, exercise, and diet and will be assessed using the Pittsburgh Sleep Quality Index [37], the International Physical Activity Questionnaire–Short Form [38], the Food Behavior Checklist [39], the 36-Item Short Form Health Survey [40], and 2 self-developed scales (subjective assessment of overall health and impairment owing to overall health).

The measures and tasks used to assess the primary outcome, cardiometabolic health, are described in the following sentences:

1. Everyday Discrimination Scale: the participants will complete a Spanish version of the Everyday Discrimination Scale [36], a 9-item scale that assesses the frequency and the attribution of discrimination experiences (eg, In your day-to-day life, how often are you treated with less respect than other people are?) to assist them in identifying a discrimination experience to speak about in the SOC task. Items are rated on a scale of 0 (never) to 5 (almost every day), with higher scores indicating a higher frequency of discrimination experience. Previous studies have demonstrated good reliability and validity in HL samples [41].

2. SOC task: after a 2-minute baseline task (sitting with no stimuli), the participants will be asked to select an experience of discrimination to focus on for a SOC task. To help them do this, the participants will complete a brief questionnaire of common discrimination experiences, followed by a 5-minute interview to help them select among the experiences reported on the questionnaire. This cardiovascular reactivity task is modeled after a SOC task previously used in our laboratory [35], modified to be ecologically relevant to this population. The SOC task will ask the participants to speak for 4 minutes about the discrimination experience, focusing on the thoughts and feelings they had. The participants will then complete a 2-minute resting-recovery task wherein they will speak about a positive memory. The prompt for the SOC task is as follows (prompt translated to Spanish and available in English and Spanish, based on participant’s preference):

For the next four minutes, I would like for you to please discuss in detail your experience during this time that you have identified when you felt [insert discrimination experience here]. Please discuss your thoughts, feelings, hopes, and concerns about the experience. Remember, there are no right or wrong answers, so please say whatever comes to mind. Your job is to talk continuously about anything that comes to mind about this experience for the 4-minute period. We will record your responses because how you are thinking and feeling about this experience is very important to us.

3. Pittsburgh Sleep Quality Index: the participants will report on their sleep quality using the Spanish version of the Pittsburgh Sleep Quality Index [42], a 10-item measure that assesses sleep quality and duration. Items (eg, How many hours of actual sleep do you get at night—this may be different than the number of hours you spend in bed?) are rated on a scale of 0 to 3, whereby higher scores reflect more sleep disruption. Previous studies have demonstrated good reliability and validity in HL samples [43].

4. Food Behavior Checklist: the participants will report on their diet using the Food Behavior Checklist for Spanish speakers [39], a 16-item questionnaire that measures basic dietary behaviors, including the frequency of fruit, vegetables, juice, and low-fat dairy consumption; food insecurity; shopping; and cooking techniques. Previous studies have demonstrated good reliability and validity in HL samples [44].

5. Thirty six-Item Short Form Health Survey: the participants will report on their overall health using a Spanish version of the 36-Item Short Form Health Survey [40], a 36-item quality of life measurement that assesses 8 health-related domains, including physical functioning, role limitations because of physical problems, bodily pains, general health perceptions, vitality, social functioning, role limitations because of emotional problems, and perceived mental health. Previous studies have demonstrated good reliability and validity in HL samples [45].

6. Subjective assessment of overall health: the participants will report on their subjective assessment of their overall health by answering a 2-item scale designed for this study. Items assess perceptions of health (eg, Compared with men or women of your age, how would you define your health?) and are rated on a scale of 0 (bad) to 5 (excellent).

7. Impairment owing to overall health: the participants will report on impairments owing to their overall health by answering a 2-item scale designed for this study. Items assess behaviors related to health (eg, During the past 3 months, how many times have you missed school or work for physical or health problems?) and are rated on a scale from 0 (never) to 5 (>10 times).

8. International Physical Activity Questionnaire—Short Form: the participants will report on their exercise habits using a Spanish version of the International Physical Activity Questionnaire–Short Form [38], a 7-item scale that assesses the duration and intensity of physical activities undertaken over the previous 7 days, including the number of hours engaged in physical activity at different intensities, including walking, moderate-intensity activities, and vigorous-intensity activities.

**Table 1 table1:** Outcomes: constructs and measures assessed.

Outcomes and constructs			Measures assessed

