**Methods:**

We will recruit a sample of 80 CSPs from community health agencies serving low-income HL populations. Participating CSPs will be randomized into an experimental or a waitlist control. Participants will complete 1 or 2 baseline assessment batteries (before the intervention), depending on the assigned group, and then complete 2 more assessment batteries following the 4-week RS intervention (after the intervention and at a 3-mo follow-up). The RS intervention consists of guided reflections on positive moments of connection with others. Electrocardiogram data will be obtained from a wearable device (Polar Verity Sense or Movisens) to measure heart rate variability. The primary outcome is cardiometabolic health, consisting of cardiometabolic risk (obtained from heart rate variability) and cardiometabolic health behaviors. The secondary outcomes include CSPs’ threats to leaving the workforce (assessed via psychological well-being), intervention acceptability, and CSPs’ delivery of cardiometabolic health programming to the community (exploratory). Analyses of covariance will be used to examine the effects of RS on cardiometabolic health and on CSPs’ threats to leaving the workforce, comparing outcomes at baseline, postintervention, and at follow-up across participants in the experimental versus waitlist group.

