### Data Analytic Plan

Descriptive statistics will be used to analyze the demographic characteristics of our sample population. A series of analyses of covariance will be conducted to examine the effects of RS on HRV, health behavior, psychological well-being, threats to CSPs leaving the workforce, and the reach of CSPs’ cardiometabolic health programming. We will compare outcomes at baseline, immediately postintervention, and at the 3-month follow-up across participants in the experimental versus waitlist group. HRV at baseline will be included as a covariate in analyses examining HRV, and all analyses will examine a range of potentially confounding covariates for potential use in analyses (eg, age, BMI, and socioeconomic status; those that are significantly associated with key study variables will be included as covariates in hypothesis testing). Effect sizes will be examined in all analyses. With a sample size of 80, it will be possible to detect small-to-moderate effects (yielding an effect size *d*=0.24) of RS on the CSPs’ cardiometabolic health, threats of CSPs leaving the workforce, and the delivery of cardiometabolic health programming. As stated in the *Eligibility Criteria and Recruitment* section, our goal is not to detect statistically significant effects but rather to look for effect sizes to inform future studies.

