### Limitations

We anticipate that our study has limitations, some associated with the fact that the study will be conducted virtually, with participants usually at home or at their job location. Although remote sessions have advantages, it has been reported that it may be necessary to contact additional participants to reach enrollment and compliance goals in remote (vs in-laboratory) studies [60]. This is in addition to the fact that overall research recruitment has been affected since the pandemic. Likewise, the technology (devices, programs, and internet connection) needed to conduct remote studies can be unreliable, as has been found in previous studies [60]. Regarding the cardiovascular data, technical difficulties with the wearable devices and logistical issues in their delivery might result in missing ECG data, particularly given that the participants themselves will be tasked with deploying the devices. Given that one of the broader goals of the project is to provide information regarding the feasibility of the approach, any information yielded through this effort will be useful. However, missing data will preclude us from being able to understand the impact of RS on cardiometabolic health. Finally, we recognize that the planned analyses may be considered simple, yet this is what the sample size will afford. Furthermore, the data we can collect is limited to that which is feasible for the community agencies with whom we collaborate. These compromises accompany community-engaged work.

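### HRV comes from either of two devices worn at different body sites, and the analysis plan names no device term: a minor loss of precision that a pre-specified covariate would remove

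*Protocol article*

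**What the plan says.** All places are in the Protocol article.

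- **Role of HRV.** Primary Outcomes makes HRV the cardiometabolic-risk component of the primary outcome: "Cardiometabolic risk will be measured via HRV in response to a stressor task". Self-reported health behaviours form the other component.
- **Devices.** The same section says "ECG data will be recorded using a Polar Verity Sense heart rate monitor or Movisens device", described as "small wearable devices that the participants will place in their arm or chest, respectively". The abstract (Methods) leaves the choice equally open: "Electrocardiogram data will be obtained from a wearable device (Polar Verity Sense or Movisens) to measure heart rate variability".
- **One variable.** "Vagally mediated HRV will be calculated from the variability of the interbeat intervals obtained from electrocardiogram (ECG) data". No distinction by device is made at this step.
- **Model.** The Data Analytic Plan specifies analyses of covariance, in which "HRV at baseline will be included as a covariate in analyses examining HRV". Further covariates come from an open list of examples (age, BMI, socioeconomic status), and "those that are significantly associated with key study variables will be included as covariates in hypothesis testing". Device is not among the examples.
- **Device problems.** Limitations expects that "technical difficulties with the wearable devices and logistical issues in their delivery might result in missing ECG data". Comparability of the two devices is not discussed there.

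**The concern.** Two instruments, worn at two body sites and put on by the participants, feed one primary-outcome variable. If one reads systematically higher than the other, that difference becomes unexplained variance in HRV unless the model accounts for device.

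The stated covariate rule does not ensure that it will. Baseline HRV absorbs part of a constant offset, but not all of it. Device itself could enter only by being chosen as a candidate and then reaching significance, and with 80 participants a moderate offset can fail that test. Whether a known feature of the measurement enters the model should not depend on a test in the same data.

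What is at stake is precision. The trial's declared purpose is to estimate effect sizes for a later, adequately powered trial, so avoidable noise in the HRV estimate carries over into that trial's planning.

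**Working it through.** **Inputs from the document.** n = 80, two devices, analysis of covariance with baseline HRV. The article gives no figure for device share, device agreement or switching, so there is no stated figure to reproduce. Its one design figure, d = 0.24, is not used here.

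**Assumptions.** 40 per arm; correlation between baseline and outcome r = 0.6; half the participants on each device; device independent of arm; offset δ between devices of 0.5, 1.0 or 1.5 within-device SD; a share s whose outcome device differs from their baseline device.

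**Formulas.** With within-device variance 1 and the offset left out of the model:
- variance of HRV at each visit: V = 1 + δ²/4
- covariance of baseline and outcome: C = r + (δ²/4)(1 − 2s)
- residual variance: R = V − C²/V
- residual variance with device modelled: 1 − r² = 1 − 0.36 = 0.64
- variance ratio for the intervention effect: R / 0.64

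**Each participant keeps one device (s = 0).**

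| δ | V | C | R | Ratio |
|---|---|---|---|---|
| 0.5 | 1.0625 | 0.6625 | 1.0625 − 0.4389/1.0625 = 0.649 | 1.01 |
| 1.0 | 1.25 | 0.85 | 1.25 − 0.7225/1.25 = 0.672 | 1.05 |
| 1.5 | 1.5625 | 1.1625 | 1.5625 − 1.3514/1.5625 = 0.698 | 1.09 |

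The rise is about 1% to 9%. At δ = 1 the standard error of the effect goes from √(2 × 0.64/40) = 0.179 SD to √(2 × 0.672/40) = 0.183 SD. In sample-size terms, 80 participants are worth 80/1.05 ≈ 76. Chance imbalance in device between arms is already part of these figures and is not a further harm.

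**Switching (s = 0.2, δ = 1).** C = 0.6 + 0.25 × 0.6 = 0.75, and R = 1.25 − 0.5625/1.25 = 0.80. The ratio is 0.80/0.64 = 1.25, so 80 participants are worth 80/1.25 = 64. This case also needs the baseline covariate to come from an earlier visit. If it is a resting recording from the same session, covariate and outcome normally share a device and the s = 0 table applies.

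**Simulation check.** Two independent runs of 3,000 trials per cell compared the model without device terms to the model with them. For δ = 0.5/1.0/1.5 and no switching, one gave 1.00/1.04/1.07 and the other spanned 1.01 to 1.08. At 20% switching and δ = 1 they gave 1.22 and 1.24. These agree with the formulas. With device terms the variance was 1% to 3% above the no-offset level, so at δ = 0.5 without switching the term roughly breaks even.

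**Would the screen catch the offset?** Take a two-sided 5% test of device against HRV, normal approximation.
- Even split: standard error √(1/40 + 1/40) = 0.224. Power at δ = 0.5 is Φ(0.5/0.224 − 1.96) = 61%; at δ = 1 it is Φ(1/0.224 − 1.96) = 99%.
- 8 participants on one device and 72 on the other: standard error √(1/8 + 1/72) = 0.373. Power is 27% at δ = 0.5 and 76% at δ = 1.

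The screen would therefore miss a moderate offset fairly often. It would usually find a large one, provided device is put forward as a candidate.

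**The case against.** **The covariate list is open, and this is a condensed article.** A reader might infer that device is excluded from the model, or that participants are moved freely between devices. The text says neither. The list gives examples only, and device assignment and logging may be set out in a full protocol or analysis plan not shown. This objection stands, so the point is confined to what the article does fix: two devices, one variable, and a significance rule for every covariate except baseline HRV.

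**Switching is not documented.** It is tempting to read the expected device and delivery trouble as meaning that one device will be replaced by the other, and to quote the larger variance figures as the likely harm. Limitations speaks only of missing readings. The word joining the two devices fits one device per participant, per agency or per period just as well. This stands.

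**The meaning of baseline HRV is not settled.** It may be the pre-intervention visit or the resting recording before the stressor in the same session, since the SOC task begins with a 2-minute resting baseline. On the second reading, a change of device between visits does not break the link between covariate and outcome. This stands too.

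**The sensors may differ in kind.** A reader might conclude that the arm device does not record ECG, or is the worse of the two. The documents call both signals ECG and do not describe the sensors, so nothing here supports relabelling the signal or restricting analysis to the chest device.

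**Randomisation protects the comparison.** It prevents systematic bias if device is independent of arm. It does not remove the added variance, so the precision point survives.

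**Conclusion.** The point holds as a minor precision improvement. HRV from two devices is treated as one variable, and the stated covariate rule brings device in only if it passes a significance screen.

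Under the assumptions shown, the cost is about 1% to 9% in the variance of the HRV effect when participants keep one device, and less if one device predominates. A cost of about 25% requires a 1 SD offset, 20% switching and a baseline covariate taken from an earlier visit; none of these is documented, so it is a conditional upper scenario, not an expected harm. The true offset could also be near zero, in which case nothing is lost by the present plan.

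No bias in the comparison of arms is claimed, and the health-behaviour component of the primary outcome is unaffected.

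**What to change.** In the Data Analytic Plan:

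1. Pre-specify device as a fixed covariate in every HRV model, outside the significance screen, using the device recorded for each session. Where a participant's baseline and outcome devices differ, include a term for each.
2. Add a sensitivity analysis of the HRV effect by device. A covariate corrects a difference in mean level only, so this is also where a difference in scale or noise would show.

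For visits still to come, keep each participant on the same device where possible. The Results section reports 79 enrolled by November 2023 and data collection expected until May 2024, so this can help only with remaining visits; the model term and the sensitivity analysis carry most of the benefit.

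The cost is one or two degrees of freedom and one extra analysis. If the offset is small and nobody switches, the term gains essentially nothing, but it loses very little. The fix depends on the device having been recorded for each session; if it was not, it should be recovered from the data files where possible.
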